**Methods:**

The study is an interventional, two-arm, randomized controlled trial. During a 2-year period, a total of 132 families will be included. Participants will be recruited from East-Denmark. Inclusion criteria are (1) TBI or tSCI, (2) ≥ 18 years of age, (3) ≥ 6 months to ≤ 2 years since discharge from hospital, (4) ability to understand and read Danish, (5) cognitive abilities that enable participation, and (6) a minimum of one family member actively involved in the survivor’s life. Exclusion criteria are (1) active substance abuse, (2) aphasia, (3) prior neurologic or psychiatric diagnose, and (4) history of violence. Within each disease group, families will be allocated randomly to participate in an intervention or a control group with a ratio 1:1. The intervention groups receive the family intervention consisting of eight sessions of 90 min duration. Families in the control groups receive 2 h of psychoeducation. All participants complete questionnaires on QoL, self-perceived burden, family dynamics, problem-solving strategies, mental health, and resilience at pre-intervention, post-intervention, and 6-month follow up.

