## Methods

### Trial design

This is a two-arm RCT of a manualized family intervention conducted in two different disease groups: (1) patients with TBI and (2) patients with tSCI, participating with a minimum of one family member actively involved in the patient’s life. The duration of the study is from October 2018 to October 2021 with an inclusion period of 2 years. The trial was developed according to the guidelines for Standard Protocol Items: Recommendations for Interventional Trials (SPIRIT) statement [43] (see Additional file 1 and Fig. 1), and will be reported as stated in the Consolidated Standards of Reporting Trials statement for reporting randomized trials of social and psychological interventions (CONSORT-SPI) [44].

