##### Primary and secondary outcome

The effect of the family intervention will be measured by self-report questionnaires. The outcome measurements are outlined in Table 2 and will be measured at baseline, post-intervention, and at 6-month follow up (Table 2).

**Table 2 Tab2:** Primary and secondary outcome measures

Domain	Assessment	Test tool (outcome measure)	Administered by
Quality of life (QoL)	Generic QoL	Short Form-36 (SF-36) [9, 10, 52, 53]	All participants
	The patient’s disease-specific QoL	QoL after Brain Injury (Qolibri) [54]	Participants with TBI
		International Spinal Cord Injury QoL Basic Data Set [55]	Participants with tSCI
Self-perceived burden	General burden, isolation, disappointment, emotional involvement, environment	Caregiver Burden Scale (CBS) [12, 56]	Caregivers
	Physical, emotional and financial burden	Self-Perceived Burden Scale (SPB) [57]	Participants with TBI or tSCI
Family dynamic	Flexibility	Family Adaptability and Cohesion Evaluation Scales-IV (FACES-IV) [58]	All participants
	Cohesion		
	Communication		
Problem-solving abilities	Confidence	Problem-Solving Inventory (PSI) [59]	All participants
	Personal control		
	Approach-avoidance		
Mental health	Depression	Patient Health Questionnaire-9 (PHQ-9) [60]	All participants
	Anxiety	Generalized Anxiety Disorder-7 (GAD-7) [61]	
	Satisfaction with life	Satisfaction with Life Scale (SWLS) [62]	
Relationship	Relationship to relatives	Relationship Assessment Scale (RAS) [63–65]	All participants if a dyad
Resilience	Resilience and robustness	The Resilience Scale for Adults (RSA) [66]	All participants

All participants in the two groups will complete self-report questionnaires to collect generic QoL data as the primary outcome measurement, and self-perceived burden, family dynamics, problem-solving strategies, mental health, and resilience as secondary outcome measurements. In cases where the family consists of a dyad, e.g. a married couple, mother and daughter etc., rather than several family members, the Relationship Assessment Scale (RAS) [63–65] will be completed as a supplement.

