### Sample size

Preliminary statistical power calculations have been carried out to allow us to detect any group effect (intervention versus control in the TBI and tSCI group, respectively) on the primary outcome variable, i.e. generic QoL data assessed by the Short Form-36 (SF-36) [9, 10]. Numbers of participants required in the study were calculated based on the Mental Component Summary (MCS) of the SF-36 [52, 53]. As no studies have been carried out in Denmark using the SF-36 in patients with a traumatic injury, a Norwegian study [70] was used for the sample size calculations. In the Norwegian study, a score of 43.8 (SD 12.5) was reported among patients with moderate to severe TBI. Based on a confidence level of 95%, a power level of 80%, and a significant difference of 5 points between the intervention and control group, it will be necessary to recruit 182 participants to each arm of the trial i.e. the TBI and tSCI arms. To account for a 10% drop-out rate, 400 participants in total must be included.

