### Randomization

#### Sequence generation and allocation concealment mechanism

Within each disease group, families will be allocated randomly to the intervention group or the control group with an allocation ratio of 1:1. The Sealed Envelope application will be used to generate random allocation sequences: this is an online software application for randomizing patients into clinical trials [71]. The random allocation sequence will be generated and concealed from the employees in the project. The families will consecutively be allocated to each group. Two arms for the TBI group and two arms for the tSCI group will be created with 66 families in each disease-specific group. The randomization will be conducted in blocks of 22, which increases the likelihood that the intervention groups and the control groups will have the exact same number of participants, even in the case of recruiting fewer participants than expected. When entering the unique family ID number in Sealed Envelope, the application randomizes the family to either the intervention group or the control group.

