#### Analytical methods

Data will be stored in a password-protected electronic database, REDCap [72], which is a web-application for building and managing databases. All participants will be assigned a unique trial ID number and all demographic data, and data from the files and questionnaires will be stored in the database to ensure quality of the data. The nurses will be responsible for this part of the data management process.

The following analyses will be conducted in each arm of the trial. First, the baseline level of the primary outcome, generic QoL data, will be compared between groups using one-way analysis of variance (ANOVA). If there are significant differences at baseline, we will adjust for these in the following analyses. Intention-to treat (ITT) analyses will be performed to examine the effect of the family intervention using repeated measures ANOVA (rANOVA), with “time” as the repeated measurement. The comparison between the intervention group and control group in each disease group will be the between-group factor. Baseline characteristics will be assessed and compared between groups using one-way ANOVA, and we will adjust for these characteristics if necessary.

Little’s Missing Completely at Random (MCAR) approach will be applied for analysis of group allocation and of disease group to investigate whether drop-outs or missing data are associated with one of these parameters. Data analysis will be completed using STATA.

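### Families are randomised and treated together, but neither the sample size nor the repeated measures ANOVA allows for correlation within families

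*Protocol article*

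**What the plan says.** **Unit of randomisation.** Under Sequence generation and allocation concealment mechanism, the protocol states: "Within each disease group, families will be allocated randomly to the intervention group or the control group with an allocation ratio of 1:1". The numbers follow in the same section: "Two arms for the TBI group and two arms for the tSCI group will be created with 66 families in each disease-specific group". The abstract agrees: "During a 2-year period, a total of 132 families will be included".

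**Who is in a family.** Trial design has each patient "participating with a minimum of one family member actively involved in the patient’s life", so a family contributes at least two people. Survivor and relatives attend the same sessions.

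**Who supplies the primary outcome.** Primary and secondary outcome: "All participants in the two groups will complete self-report questionnaires to collect generic QoL data as the primary outcome measurement".

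**Sample size.** It rests on the SF-36 Mental Component Summary with SD 12.5, a 5-point difference, 95% confidence and 80% power, and concludes that "it will be necessary to recruit 182 participants to each arm of the trial i.e. the TBI and tSCI arms". Adding 10% for drop-out gives 400 participants in total. No family size, ICC or design effect appears.

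**Analysis.** Analytical methods names a repeated measures ANOVA with time as the repeated measurement. On treatment it says: "The comparison between the intervention group and control group in each disease group will be the between-group factor". It names no family term, clustered variance or family-level summary.

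**The concern.** Relatives who live with the same injury and go through the same sessions are unlikely to give independent quality-of-life scores. The trial's own hypothesis, in Background and objectives, is that better caregiver mental health improves support and in the end the survivor's quality of life. That is a statement that relatives' scores move together.

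If an analysis treats relatives as independent, its standard errors for comparisons between randomised families are too small, its confidence intervals too narrow and its p-values too favourable. If it accounts for families, the effective sample is smaller than the head count, and the power statement is optimistic. According to the Discussion, an effect would lead to a permanent programme and wider roll-out, so the error rate of the primary comparison matters.

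**Working it through.** **Inputs from the protocol.** SD 12.5; difference 5 (standardised 0.4); two-sided 5% (read from the 95% confidence level); 182 participants per disease group, so 91 per treatment group at 1:1; 66 families per disease group, so 33 per treatment group; 400 participants in 132 families, so 400/132 = 3.03 per family.

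**Assumed, because the documents do not give it.** Within-family ICC of 0.1, 0.2, 0.3 or 0.4. Family size m = 3 (rounded from 3.03), with m = 2 as the minimum.

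**1. The plan's own figure.** n per group = 2 × (1.96 + 0.842)² × 12.5² / 5² = 98.1, so 99 per group and 198 per disease group, not 182. An SD of 12.0 would give 91 per group, but the stated SD is 12.5. At 91 per group, 0.4 × √(91/2) = 2.698 and 2.698 − 1.96 = 0.738, which is a power of 77%. This shortfall exists before any clustering. The drop-out step is consistent: 2 × 182 = 364, and 364 × 1.1 = 400.4.

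**2. Can the 182 be independent?** No. There are only 66 families per disease group, so relatives must count as separate units for the figure to be reached.

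**3. Design effect, true size and power.** DE = 1 + (m − 1) × ICC. True size of a naive 5% between-arm test = 2 × [1 − Φ(1.96/√DE)]. Power of a valid unadjusted single-visit comparison: t-test with 91/DE per group.

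| m | ICC | DE | True size | Power |
|---|---|---|---|---|
| 3 | 0.1 | 1.2 | 7.4% | 69% |
| 3 | 0.2 | 1.4 | 9.8% | 62% |
| 3 | 0.3 | 1.6 | 12.1% | 56% |
| 3 | 0.4 | 1.8 | 14.4% | 51% |
| 2 | 0.1 | 1.1 | 6.2% | 73% |
| 2 | 0.2 | 1.2 | 7.4% | 69% |
| 2 | 0.3 | 1.3 | 8.6% | 65% |
| 2 | 0.4 | 1.4 | 9.8% | 62% |

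The dyad rows hold 91 participants per group fixed. That would take 91 families per disease group, not 66.

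**4. The time-by-arm test.** This test uses within-person contrasts, so a family effect that is constant over visits cancels. Simulation of the ANOVA under no effect (66 families of three, three visits, correlation 0.6 between a person's visits) gives rejection rates near 5% at every ICC from 0.1 to 0.4. The arm main effect stays inflated in that case.

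If relatives' visit-to-visit changes carry the same ICC, the variance of the contrast is inflated by DE. With three visits the test has two numerator degrees of freedom, and its large-sample size is 0.05^(1/DE): 8.2%, 11.8%, 15.4% and 18.9% for DE 1.2, 1.4, 1.6 and 1.8. Simulations of the same set-up agree, with the last value between 18% and 20%.

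**5. Power from the families actually planned.** With 33 families of 3.03 per group (100 people), no drop-out and the normal approximation, power is 80.7% at ICC 0 and 73.2%, 66.5% and 60.6% at ICC 0.1, 0.2 and 0.3. With 10% lost it is 76.5%, 68.7%, 61.9% and 56.2%. If all families were dyads (66 people per group, none lost), it would be 63.2%, 59.1%, 55.5% and 52.2%.

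**The case against.** **The treatment test may not be inflated.** In a repeated measures ANOVA the natural test of the intervention is time-by-arm, and a stable family effect leaves it at about 5%. This stands. A reader might infer that the planned test must exceed 5%. The documents do not support that: it needs correlated change between relatives, whose size is a second assumption. Shared sessions and the trial's causal theory make such correlation plausible but do not measure it. The protocol also does not say which ANOVA term is the test.

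**The power loss is not all due to clustering.** This stands. The fall from 80% to 77% is an arithmetic matter. Clustering accounts for the rest.

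**Baseline adjustment would restore power.** This stands in part. If baseline and follow-up correlate at 0.6 (an assumption), the variance falls by the factor 1 − 0.6² = 0.64. Power at 91 per group with families of three becomes Φ(2.698/√(0.64 × DE) − 1.96), which is 87%, 81%, 76% and 71% at ICC 0.1 to 0.4. So one cannot say that every valid analysis falls well short of 80%. The protocol's calculation takes no such credit, and it plans to adjust for baseline only if the groups differ significantly.

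**Families may be small and the ICC low.** Dyads with an ICC of 0.1 to 0.2 give a true size of only 6 to 7%. This stands as the mild end of the range.

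**An analysis plan may add clustered variance.** The article never says outright that relatives are treated as independent, and clustered standard errors would not contradict its wording. But the sample size as printed counts 182 individuals from 66 families, so the omission is in a stated method and is not just detail left for later.

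**Conclusion.** The point holds. The protocol randomises and treats families, counts and measures individuals, and makes no allowance for within-family correlation in either the sample size or the named analysis.

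The direction for the between-arm test follows from any positive ICC. The size rests on assumed values: about 7 to 14% true error for three members per family and 6 to 10% for dyads, at ICC 0.1 to 0.4. The range of about 8 to 19% for time-by-arm is conditional on correlated change.

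The 80% power is not delivered by the protocol's own inputs, and it falls further once families are accounted for in an unadjusted single-visit comparison.

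A reader might infer that one analysis suffers both problems. It does not: excess false positives belong to an analysis that ignores families, and lower power to one that respects them.

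**What to change.** **Analytical methods.** Replace the repeated measures ANOVA with one of two options:
- a linear mixed model with participant and family random effects, in which the family effect may vary by visit;
- a model with family-level cluster-robust standard errors.

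Either should include arm, visit, arm-by-visit, baseline score and role (survivor or caregiver). A random family intercept alone is not enough, because it does not represent correlated change, which is the case in which the time-by-arm test goes wrong. Name the contrast that is the primary test.

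**Sample size.** State the assumed family size m and ICC, apply 1 + (m − 1) × ICC, and correct the arithmetic that links SD 12.5 to 182. Then restate the power that 66 families per disease group give, over a range of ICC. If credit is taken for baseline adjustment, state the assumed correlation.

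**Cost.** Revised wording and a less favourable power figure. Family ID numbers are already entered at randomisation, and Stata, which the protocol names, fits both options. No extra enrolment or data collection is needed. Trial status reports 13 families randomised when the article was written.

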Consequently, the aim of the present study is to investigate the effect of the eight-session manualized family intervention on QoL in individuals with TBI or tSCI and their family members, compared to a control group. The effect will be measured short term (post-intervention) and long term (6-month follow up). It is assumed that people who survive a traumatic injury do so in the context of their family. Therefore, a minimum of one family member, actively involved in the patient’s life, must be included in each session of the intervention. To our knowledge, the present randomized controlled trial (RCT) will be the first to evaluate the effectiveness of a manual-based family intervention to improve QoL in the entire family. This will be investigated by the following primary research question: Will the families in the intervention groups report improved QoL compared to the families in the control groups? The secondary research question is: Will the families in the intervention groups report decreased burden compared to the families in the control groups? It is hypothesized that the family intervention will lead to improved QoL and decreased burden for both the survivor of TBI or tSCI and their caregivers. Consequently, better mental health of the caregiver will improve the care and support they provide to the survivor. This improvement will ultimately improve the QoL of the survivor.

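### As written, the primary analysis combines survivors and relatives with no term for role, so a significant result alone cannot support improved QoL for both

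*Protocol article*

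**What the plan says.** The primary research question in Background and objectives is put at family level: "Will the families in the intervention groups report improved QoL compared to the families in the control groups". The hypothesis that follows it is narrower and expects "improved QoL and decreased burden for both the survivor of TBI or tSCI and their caregivers".

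Primary and secondary outcome takes the primary measure from everyone: "All participants in the two groups will complete self-report questionnaires to collect generic QoL data as the primary outcome measurement".

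The Sample size section works on the SF-36 Mental Component Summary (MCS). Its source for mean and SD is a patient sample: "a score of 43.8 (SD 12.5) was reported among patients with moderate to severe TBI". It continues "Based on a confidence level of 95%, a power level of 80%, and a significant difference of 5 points between the intervention and control group" and arrives at 182 participants for each of the TBI and tSCI groups, and 400 in total after 10% drop-out. The randomization section plans four groups by disease and treatment, "with 66 families in each disease-specific group", allocated 1:1.

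Analytical methods specifies the effect analysis "using repeated measures ANOVA (rANOVA), with “time” as the repeated measurement", and adds: "The comparison between the intervention group and control group in each disease group will be the between-group factor". It allows adjustment for baseline differences where needed. Role is not named as a factor, a stratum or the basis of a separate analysis.

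The article calls the two disease groups arms. Below, arm means intervention or control.

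**The concern.** The hypothesis concerns two kinds of people and the analysis gives one arm effect across both. A family contributes one survivor and a variable number of relatives, so that effect is a weighted average in which relatives carry most of the weight. It can be significant because relatives improved, with nothing shown for survivors. It can also miss a real effect confined to survivors.

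This matters for how a positive result is used. The Background faults earlier caregiver interventions because their effect on the survivor is unclear, and the Discussion ties a permanent programme, and more help for patients and their families, to an effect on the primary outcome. A pooled estimate alone would leave the same question about the survivor open.

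**Working it through.** **1. Do survivors and relatives enter one comparison?** Each disease group has 66 families, hence 66 survivors, or 33 per arm. The analysed number is 182 per disease group, or 91 per arm. 182/66 = 2.76 analysed persons per family (400/132 = 3.03 enrolled). The target can be met only by counting relatives with survivors.

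**2. The plan's own sample size.** Inputs from the Sample size section: difference 5, SD 12.5, power 80%, 5% level (two-sided assumed).
- n per arm = 2 × (1.96 + 0.84)² × (12.5/5)² = 98.1 with unrounded normal quantiles, so 99 per arm and 198 per disease group. The stated 182 is not reproduced.
- SD 12 gives 90.4, so 91 per arm, which is exactly 182.
- With 91 per arm and SD 12.5, the standard error is 12.5 × √(2/91) = 1.85 and power is about 77%, before any allowance for clustering in families.
- Drop-out: 2 × 182 = 364, and 364 × 1.1 = 400.4, which matches the stated 400.

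**3. Weight of survivors in the pooled effect.** If all 66 survivors are analysed, their share is 66/182 = 0.363. If 10% of them drop out, it is 59.4/182 = 0.326.
- Pooled effect = share × survivor effect + (1 − share) × caregiver effect.
- Survivor effect 0 and pooled effect 5: caregiver effect = 5/(1 − 0.326) = 7.4 to 5/(1 − 0.363) = 7.8 points.
- Caregiver effect 0 and survivor effect 5: pooled effect = 0.326 × 5 = 1.6 to 0.363 × 5 = 1.8 points.
- Significance threshold at 91 per arm: 1.96 × 1.85 = 3.63 points. With no survivor difference, an observed caregiver difference of 3.63/0.674 = 5.4 to 3.63/0.637 = 5.7 points reaches it.

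**4. What the trial can say about survivors alone, per disease group.** Two-sample t-test, SD 12.5, difference 5, one time point, no baseline adjustment:

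| Survivors per arm | Power |
|---|---|
| 33 | 36% |
| 30 (after 10% drop-out) | 33% |

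The 95% CI half-width at 33 per arm is 2.00 × 12.5 × √(2/33) = 6.1 points.

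Baseline adjustment multiplies the residual SD by √(1 − r²), where r is the correlation between baseline and follow-up. The article gives no r. For an assumed r of 0.5 to 0.8, power is 46% to 76% at 33 per arm and 42% to 72% at 30.

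**5. Difference between the role-specific effects.** With 30 survivors and 61 caregivers per arm, treated as independent, the standard error is 12.5 × √(2/30 + 2/61) = 3.94. Power for a 5-point difference in effect is about 24%.

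Steps 3 to 5 assume SD 12.5 in both roles and no within-family correlation. Step 3 and the first part of step 4 also treat the comparison as one at a single time point.

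**The case against.** The strongest reply is that the pooled estimate is the right answer to the question asked. The primary question speaks of families, the word both appears in a hypothesis and not in a decision rule, and nowhere is 80% power claimed for survivors alone. The article never says that the two roles share one model, and a fuller analysis plan could separate them. This stands in part. The pooled estimate is legitimate for the primary question, and pooling is an inference. But the article does fix the participant count and the between-group factor, and nothing in it points to a role-specific primary analysis.

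A reader might go further and infer that the pooled test is biased by unequal family sizes, or loses precision because role is omitted. The documents do not support this. Questionnaires are completed before randomization, so family size at baseline is fixed by then, and a difference between arms is chance. Baseline is one of the repeated measurements, so a constant difference in mean between survivors and caregivers largely cancels in the arm-by-time contrast.

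It is also fair to object that 36% is the low end for survivors. Baseline adjustment raises it, by an amount that depends on a correlation the article does not give.

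**Conclusion.** The point holds as a mismatch between the planned analysis and the claim for both roles. It does not show that the primary test is invalid. Followed as written, the analysis gives one arm effect per disease group in which survivors weigh about one third. About 7.5 points in caregivers and none in survivors reproduces the full planned difference, so a significant pooled result cannot by itself show benefit in survivors or in both.

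The sample-size calculation relates to the pooled comparison, and there its power is about 77% at SD 12.5 before clustering, not 80%.

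The conclusion that survivors and relatives are pooled rests on the outcome being taken from all participants, on 182 against 66, and on the factors listed. The sizes rest on the assumptions stated with the calculations.

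**What to change.** Before analysis, amend the primary model in each disease group:

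- Add role (survivor or caregiver) with arm-by-role-by-time terms, and account for correlation within families. The latter is new, because the article's analysis has no family term.
- Report the arm difference in MCS with its 95% CI for survivors and for caregivers, beside the pooled estimate.
- Limit any claim of benefit in survivors, or in both, to what the role-specific estimates and intervals support. A shared direction is not enough: with no true survivor effect, the survivor estimate is favourable about half the time.
- State that the sample-size calculation concerns the pooled comparison, with about 77% power at 91 per arm and SD 12.5 before clustering, and that power for survivors alone is lower.

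The cost is analysis and wording only. Role is already known, since some instruments differ by role and the family relationship is recorded. The downside is that role-specific intervals will be wide, about ±6 points for survivors without baseline adjustment, and the test of a difference between roles has low power, so it will be largely descriptive.

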### Limitations and generalizability

The present study will have some limitations that should be addressed. First, the study will only include families, who are willing to participate. Consequently, some families, who would fulfill our inclusion criteria, will not be included. One could speculate which families will be willing to participate in the study. Will it be families, who need help and support, or families, who have the time and resources? If a family refuses to participate, the reason for refusal will be obtained. Furthermore, as participation will be voluntary, all family members have the right to withdraw their consent if they want to quit the project. One could speculate whether families allocated to the control group will be more likely to drop out compared to families in the intervention group, because of a great desire to receive help. However, as the family intervention is very intense and time-consuming, this can also affect the risk of drop-outs in the intervention group. Therefore, prior to the allocation the nurses will inform the families about the content of the intervention in both groups both orally and in writing.

Second, most patients included in the study will have been hospitalized for specialized neurorehabilitation due to a severe traumatic injury. However, patients with severe cognitive disabilities or severe aphasia will be excluded, as patients with such disabilities will not be able to participate fully in the family intervention. This will affect the generalizability of the study, as patients with the most severe injuries or sequela will be excluded.

Third, participants will be recruited from only two clinics in Denmark - one clinic for patients with TBI and one clinic for patients with tSCI. This warrants caution with respect to generalizing the results and could potentially limit the external validity. However, as the two clinics have an uptake area covering the whole eastern part of Denmark with a total of almost 2.6 million inhabitants [45], the representativeness and generalizability is expanded.

Finally, due to the study design, it will not be possible to blind the participants or the neuropsychologist to the allocation. However, the researchers responsible for statistically analysing baseline, post-intervention, and follow-up questionnaire data will not know to which group the families were allocated.

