### Interpretation

For families allocated to the intervention group, there can be some benefits and harms to consider. Participating in the family intervention may be costly for some families in terms of resources and time rather than an opportunity to receive support and help. This may influence the willingness to participate in the 8-week intervention, as participation may seem too time-consuming. To minimize the burden for the families, the neuropsychologist and nurses will be flexible in scheduling the sessions and the location of the intervention, e.g. if the family members have work or study obligations, then it will be possible to schedule a late session, and if the patient suffers from severe fatigue, then the intervention can be offered at home. Furthermore, the families can have transport expenses reimbursed and the intervention is free of charge.

For families allocated to the control group, there can be some ethical considerations. All families are carefully informed about the study design prior to inclusion, including the information that the randomization to either the intervention group or the control group is 50:50. However, it is possible that families who are willing to participate in the project hope to be allocated to the intervention group. In the worst case, families allocated to the control group may feel rejected, as they had high hopes of receiving help and support. This may harm the family and make them withdraw their consent and quit the project. However, the families allocated to the control group will be offered one psychoeducational session with a neuropsychologist.

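### Testing missingness against allocation and disease group cannot vouch for the treatment comparison when similar numbers leave each arm for different QoL-related reasons

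*Protocol article*

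**What the plan says.** Under Analytical methods, the effect is examined by intention to treat "using repeated measures ANOVA (rANOVA), with “time” as the repeated measurement", separately in each disease group. Baseline QoL enters as an adjustment only if the groups differ significantly at baseline. One check on missing data is named: Little's MCAR "approach will be applied for analysis of group allocation and of disease group", in order "to investigate whether drop-outs or missing data are associated with one of these parameters". No consequence is attached to either result.

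Limitations and generalizability discusses who might leave. For the control arm: "One could speculate whether families allocated to the control group will be more likely to drop out compared to families in the intervention group", the suggested reason being an unmet wish for help. For the other arm: "as the family intervention is very intense and time-consuming, this can also affect the risk of drop-outs in the intervention group". Interpretation adds that control families may feel rejected: "This may harm the family and make them withdraw their consent and quit the project". No passage says whether people with high or low QoL would be the ones to leave.

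**The concern.** The article gives a different possible reason for leaving in each arm. The two pressures could produce similar drop-out rates while removing different kinds of people. The stated check asks whether missingness goes with arm or with disease group. It does not ask whether leaving depends on QoL differently in the two arms, and that dependence is what biases the comparison. At equal rates there is no association with arm to find. The outcome is self-reported and participants know their allocation, so differential selection deserves a check that can respond to it. What is at stake is how much weight a non-significant Little test can carry.

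**Working it through.** **Inputs from the article.** Target difference 5 points on the SF-36 Mental Component Summary (MCS), SD 12.5, 10% drop-out and 400 participants in total (Sample size); 1:1 allocation within each disease group (Randomization). Hence 400 / 2 = 200 per disease group and 200 / 2 = 100 per treatment arm. The article gives no operating figure for the missing-data check, so there is none to reproduce.

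**Assumptions not in the article.** True effect 0; baseline-to-follow-up correlation ρ = 0.6; drop-out equal in the two arms, at 10% or 20%; low scorers leave control and high scorers leave intervention, with log-odds 0.5 or 1.0 per SD; participants independent (family clustering ignored); 3,000 to 4,000 simulated trials per scenario. A two-visit change score stands in for the group-by-time contrast of the rANOVA.

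**Step 1: why the pooled test sees nothing.** Little's statistic is d² = Σ n_j (x̄_j − μ)′ S⁻¹ (x̄_j − μ), summed over the missing and observed patterns. Let m people leave each arm, control leavers lying d below the mean baseline and intervention leavers d above it.
- Arm: the intervention share among leavers is m / 2m = 1/2, the same as in the whole sample.
- Baseline score: the mean deviation of leavers is (−m·d + m·d) / 2m = 0.

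Both components vanish in expectation, whatever the size of d.

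**Step 2: rejection rates at the 5% level.** With equal rates and opposite selection, Little's test on arm and baseline score rejects in about 5–10% of trials when leaving depends on baseline, and in 6–7% when it depends on the post-treatment score. Using arm alone (ρ = 0.5, log-odds 1), it rejects in 5.4% at 10% drop-out and 5.1% at 20%.

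**Step 3: bias if leaving depends on baseline.** Let D be the completers' difference in baseline score (intervention minus control). Their follow-up difference is R = ρD, so D = R / 0.6. The change-score bias is R − D. The baseline-adjusted bias is R − 0.6·D = 0.

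| Drop-out, log-odds | R (simulated) | D = R/0.6 | R − D | Change score, simulated |
|---|---|---|---|---|
| 10%, 0.5 | −0.74 | −1.23 | +0.49 | +0.48 |
| 10%, 1.0 | −1.35 | −2.25 | +0.90 | +0.89 |
| 20%, 0.5 | −1.44 | −2.40 | +0.96 | +0.94 |
| 20%, 1.0 | −2.58 | −4.30 | +1.72 | +1.73 |

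Simulated baseline-adjusted bias was 0.00 to −0.01, with type I error 4.5–5.5%. Across repeat runs the change-score range is about +0.5 to +1.8.

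**Step 4: bias if leaving depends on the post-treatment score.** Selection now acts on the follow-up score, so the follow-up difference is D and the baseline difference is ρD. Change-score bias ≈ (1 − 0.6)D = 0.4D, giving −0.49, −0.90, −0.96 and −1.72. Baseline-adjusted bias ≈ (1 − 0.6²)D = 0.64D, giving −0.79, −1.44, −1.54 and −2.75. Simulation gives about −0.5 to −1.8 and −0.8 to −3.0. The approximation ignores the effect of selection on the regression slope.

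With ρ = 0.5 and log-odds 1, type I error is 9% (change score) and 19% (adjusted) at 10% drop-out, and 20% and 53% at 20%.

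**Step 5: what the check does detect.** Testing missingness against arm flags drop-out of 25% versus 10% in 82% of trials and 15% versus 5% in 68%. It does so even when leaving is random within arm and the estimate is unbiased (bias 0.02 to 0.03). So it measures a difference in rates, not bias.

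**Step 6: a direct alternative.** In a logistic model of missingness, the arm-by-baseline term rejects, for log-odds 0.5 and 1.0, in 51% and 96% of trials at 10% drop-out and in 77% and over 99% at 20%, when leaving depends on baseline. When leaving depends on the post-treatment score, it rejects in 22–84%.

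**The case against.** The strongest reply is that the article only speculates, mainly about rates, and that a difference in rates is what the check is built to find. That stands. A reader might infer that the protocol predicts low-QoL people leaving control and high-QoL people leaving intervention; it gives no such direction. If the same kind of person left both arms at equal rates, the bias would be about 0 (0.05 points at 20% drop-out in simulation).

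A reader might also infer that a biased result would pass as clean. The article attaches no interpretation to a non-significant test, so the most that can be said is that it could. Nor is the test blind in every form. The wording would allow a run within each arm on baseline scores, which flags at least one arm in 24–96% of trials (10% under no selection). The article does not state that form.

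A third tempting reading takes the raw completer differences (R above) as the bias of the planned analysis. They are not: for a change score the sign flips, and baseline adjustment removes the bias when leaving depends on baseline. That protection is not assured, because adjustment hangs on a baseline significance test.

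Finally, the article says "If a family refuses to participate, the reason for refusal will be obtained" and mentions no reason for later drop-out. That, like any further sensitivity analysis, may sit in the full protocol or analysis plan, and is not counted as an error.

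**Conclusion.** The point holds in limited form. The named check can detect different drop-out rates. It has almost no power, about 5–10%, when similar numbers leave each arm for different QoL-related reasons. A non-significant result is therefore no basis for trusting the rANOVA.

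The possible bias depends on an unknown mechanism. Under the assumptions listed, it ranges from about 0 to 3.0 points in size, at most 3.0 / 5 = 60% of the target difference. At the planned 10% drop-out it is modest: by the arithmetic above, up to about 0.9 points for a change score, and about 1.4 points after baseline adjustment if leaving depends on the post-treatment score. All signs reverse if the selection reverses. Correlation, log-odds, equal rates, direction of selection and independence within families are assumptions, not facts from the article. The change should be made; it does not invalidate the design.

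**What to change.** Within each disease group:

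1. Replace the Little test with a logistic model of missing SF-36 MCS at each follow-up visit on arm, baseline MCS, role (survivor or caregiver) and arm-by-baseline MCS, allowing for family clustering.
2. Adjust the treatment comparison for baseline MCS regardless of any baseline significance test. This removes the bias when leaving depends on baseline. It does not do so when leaving depends on the post-treatment score, where the adjusted bias in these scenarios is larger than the change-score bias.
3. For that reason, and whatever the diagnostic shows, report one sensitivity analysis that shifts missing scores separately by arm over a pre-stated range. No test on observed data can exclude dependence on unobserved scores.

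The cost is revised wording and a little extra analysis, with no extra visits. Recording a voluntary reason for leaving would help interpretation but is optional.
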